### Study setting

This research takes place in four geographical locations in England, each of which have an PDU. To maximize generalisability, sites have been chosen where there is variation in the configuration of the PDUs across the four sites to allow comparison and ascertain the optimal PDU configuration (see Table 1).

**Table 1 Tab1:** Structural variation in Psychiatric Decision Units

Trust with PDU	Maximum Length of Stay	Capacity	Referral route
Inner city 1	48 h	5	ED (liaison), Crisis Resolution and Home Treatment Teams, Street Triage
Inner city 2	24 h	10	ED (liaison), Out of Hours Team, Approved mental health professionals team, Mental health inpatient wards, 136 Place of Safety, Community teams, including crisis resolution and home treatment teams
Inner city 3	72 h	8	ED (liaison), Street Triage
Rural Site	24 h	6	ED (liaison), Crisis Resolution and Home Treatment Teams

Referrals to PDU can be made from a range of services including ED liaison psychiatry teams, Crisis Resolution & Home Treatment teams and street triage teams. Referrals are triaged at a decision point prior to admission to the PDU. Overnight accommodation is single sex and units tend to be small, with a staff: service user ratio of at least 1:2 to allow substantial time for detailed assessment, brief intervention and onward referral/ signposting. Therapeutic work is typically cognitive or psychosocial, for example, improving resilience and solution focused approaches. Pathways from the decision unit can be either subsequent admission, discharge or forward signposting to appropriate recovery and preventative services.

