### Aims

The aim of the study is to identify the impact of psychiatric decision units on mental health crisis care pathways. We will do this by administering an interrupted time series, supplemented by a synthetic control study, using routinely collected mental health trust and emergency department data. We will produce estimates of the extent to which changes in key service parameters (e.g., informal psychiatric admissions and mental health presentations at the ED) in the pre- and post-interruption period are explained by the introduction of PDUs at each of the sites in the study, and combine the results across sites to give a generalizable effect size estimate.

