## Methods

### Study design

We will use an interrupted time series design, supplemented by a synthetic control study [32]. Adults (over 18) in psychiatric crisis in England of both sexes are eligible. The data collection periods started in November 2012 and will end on March 31st 2020. This project has been given favourable opinion from the East Midlands Leicester South Research Ethics Committee (19/EM/0226) and entry to the study is currently open. The research is funded by the National Institute of Health Research (NIHR) Health Services and Delivery Research (17/49/70). The current protocol described is version 4.0, dated 16th December 2019, and relevant parties will be informed of any important protocol modifications. The research uses aggregate service use data, and so Trusts, rather than individuals join the study. A data monitoring and ethics committee is not needed as there is no experimental intervention. The Independent Steering Committee (which includes an academic chair, a statistician, and two public and patient members) provides oversight and advice.

An interrupted time series (ITS) design, using routinely collected healthcare data, will explore change in acute and psychiatric hospital activity after the introduction of PDUs in our 4 sites, hereafter referred to as the treated trusts. Quasi-experimental methods, such as an ITS design, are appropriate when the randomisation and/or the ‘trialability’ of the intervention is limited. They are particularly well suited to evaluations of organisational interventions or changes to health care at a delivery level that target population-level health outcomes and when a time series is available, as in this instance [33, 34]. In ITS studies, data are collected at multiple time points before and after the introduction of a change or intervention; enabling detection of whether or not the change has a significantly greater effect on outcomes of interest than any underlying secular trend [35]. ITS findings primarily concern whether the level and/or slope of the outcome measurement is altered once change has been implemented. Advantages of the method include controlling for baseline variation, periodicity, cyclical trend and/or autocorrelation in the time series design, prior to examination of change effects. The number of observations is important; examining a long series of outcome measurements more readily allows analyses to track both immediate and delayed effects [36].

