For outcomes relying on count data (e.g., rate of inpatient admissions per 1000 trust catchment population), a generalized linear model for a Poisson distribution (or negative binomial model where count data is overdispersed) using a segmented approach will be fitted [34]. For each outcome, we will calculate regression coefficients corresponding to both change in level (outcome) and trend (slope) after the introduction of PDUs. In this model, the estimated parameters of interest are as follows: 1. the underlying trend prior to PDU introduction (b1); 2. the level change immediately following PDU introduction (b2); 3. the slope change from pre- to post-PDU introduction (using the interaction between time and change; b3); 4. the trend (slope change) following PDU introduction (b1_b3). External validity will be explored by examination of primary outcomes in subgroups, including, for example, gender. Graphical analysis will help to identify any stepwise change in outcome measures as a result of the introduction of PDUs and detect changes in activity patterns before and after the introduction of PDUs. We will conduct separate segmented regression analyses at each PDU site to provides individual estimates (and allow for evaluation of PDU implementation at a local level). Subsequently, to estimate overall effects, individual estimates of intervention effect will be pooled across sites (using inverse variance weights in a meta-analytical model to account for heterogeneity [49];).

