### Synthetic control study

We will use the Generalised Synthetic Control (GSC) method [50] to compare the outcomes of patients attending a treated trust after the introduction of a PDU, to that of patients attending selected control trusts. The GSC method is in the spirit of a traditional synthetic control method in that it effectively re-weights the controls units to create a so-called ‘synthetic control’ that has similar values of the outcomes and covariates in the pre-intervention period. The idea is that this similarity is assumed to extend into the post-intervention period, providing an estimate of the outcomes that would have been expected at the trust if the PDU had not been introduced. These are referred to as the counterfactual outcomes.

The approach is as follows. For each treated trust, we first select a subset of the available control trusts that are as ‘similar’ as possible to the treated trust in the period prior to the introduction of the PDU. Similarity will be assessed in terms of variables such as attendances, deprivation, patient profile and location profile, e.g. by using the NHS TRUST Peer-Finder Tool [51]. The GSC method then uses the data from the selected control group, as well as the pre-intervention data from the treated trust, to estimate a synthetic control, and hence the counterfactual outcomes for the treated unit. The difference between these counterfactual outcomes and the observed outcomes in the treated unit in the period following the introduction of the PDU is assumed to provide estimates of the causal impact of the PDU on the outcomes in the treated unit. The precision of estimates will be assessed using parametric bootstrap procedures as described in [50] to generate *P*-values and confidence intervals.

Estimates will be risk-adjusted for variables that reflect changes over time in the characteristics of the denominator population, i.e. those who are able to have the outcome. For example, when looking at the rate of ED psychiatric presentations per 1000 trust catchment, the characteristics of the trust catchment population are relevant; when looking at the proportion of 4-h psychiatric ED breaches, the characteristics of psychiatric ED presentations are relevant. Estimates of overall effect will be made using the same methods as described for the ITS analysis.

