Instrumentation [35], in which the measurement method changes during the intervention and evaluation period could also be an issue in the synthetic control study, in which we link between different datasets which cover different time periods. However, any changes in instrumentation will also be present for the synthetic control, so the change in instrumentation will balance between the two groups. The ITS design can be susceptible to fluctuating trends and cycles – we will statistically control for autocorrelation if indicated.

This study is well designed to identify changes to important service level measures of the functioning of the mental health crisis care pathway due to the PDU, allowing the trust-wide effects of PDUs to be estimated. The limitations of the ITS design are appropriately addressed by the inclusion of the synthetic control study, sensitivity analysis, and statistical methods selected. The selection of sites which have variation in PDU configuration will allow inferences to be made about the optimum design of decision units. It is possible that PDUs increase fragmentation in the crisis care pathway and do not have a beneficial effect on some or all service level measures. This study is well designed to identify such possibilities and will provide valuable information for Commissioners and trusts to address the pressure on the mental health crisis care system and will make an important contribution to the evaluation of PDUs and similar units in addressing challenges to mental health crisis care internationally.

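### Four sites that differ in several features at once cannot show which PDU configuration is optimal, although the protocol says they will

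*Protocol article*

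**What the plan says.** Only the protocol article is available here; its statistical analysis plan is not shown.

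- **Configuration.** Study setting says that sites with differing units were chosen "to allow comparison and ascertain the optimal PDU configuration". The Discussion repeats this as a property of the design: "The selection of sites which have variation in PDU configuration will allow inferences to be made about the optimum design of decision units". Table 1 gives the four configurations. The article describes no method for comparing them.
- **Overall effect, ITS.** Each site is fitted separately, and then "individual estimates of intervention effect will be pooled across sites (using inverse variance weights in a meta-analytical model to account for heterogeneity". Under Aims, the purpose is to "combine the results across sites to give a generalizable effect size estimate".
- **Overall effect, synthetic control.** "Estimates of overall effect will be made using the same methods as described for the ITS analysis". Controls are picked site by site: "For each treated trust, we first select a subset of the available control trusts". The text does not say whether these subsets may share trusts.

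**The concern.** The two statements about the best configuration are affirmative claims about what the study will deliver, so they are not details left to an analysis plan. With one unit per configuration, any difference between site effects can be put down to length of stay, capacity, referral routes, setting, or anything else particular to that trust. A reader planning a service could take a single-site contrast as evidence for a particular unit design.

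The same small number of sites bears on the pooled effect. It averages four sites chosen to differ, so heterogeneity is to be expected, and some common interval methods perform poorly with so few estimates. In the synthetic control study there is a further question: whether the four estimates are independent.

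**Working it through.** **The plan's own figure.** The only power figure, above 99% for 208 weekly points, is for a single series. With f² = 0.15 for a medium effect and alpha 0.05 (both assumed), one tested parameter and five predictors, noncentrality is 0.15 × 208 = 31.2 and power is 0.9998, so it reproduces. It does not bear on a comparison between sites or on the pooled effect; the article gives no figure for either.

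**Configuration.** Inputs from Table 1 (CRHT = crisis resolution and home treatment team):

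| Site | Stay (h) | Capacity | CRHT referral | Street triage referral | Rural |
|---|---|---|---|---|---|
| Inner city 1 | 48 | 5 | yes | yes | no |
| Inner city 2 | 24 | 10 | yes | no | no |
| Inner city 3 | 72 | 8 | no | yes | no |
| Rural | 24 | 6 | yes | no | yes |

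1. *Pairs.* There are six pairs of sites. The three inner-city pairs each differ in stay, capacity and referral routes. Inner city 2 and the rural site share the 24 h limit but differ in capacity, referral routes and setting. The other two pairs differ in all four features. No pair isolates one feature.
2. *Joint model.* Residual df = 4 − rank of the design matrix. Intercept, linear stay and linear capacity have rank 3, leaving 1 df. Adding CRHT referral gives rank 4, leaving 0. All six columns (intercept plus the five above) still have rank 4, so the effects are not identifiable.
3. *One feature alone.* Residual df = 4 − 2 = 2, and the critical t is 4.303. The smallest correlation reaching p < 0.05 is t/√(t² + df) = 4.303/√(18.51 + 2) = 0.95. Even then, the feature stays mixed with the others.

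**Pooling, k = 4** ("explore change in acute and psychiatric hospital activity after the introduction of PDUs in our 4 sites"). Simulated coverage of nominal 95% intervals: 40,000 replicates per setting, equal within-site variances, independent sites.

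| I² | DerSimonian-Laird, z | Hartung-Knapp, t(3) |
|---|---|---|
| 0 | 0.96 | 0.95 |
| 0.25 | 0.94 | 0.95 |
| 0.50 | 0.91 | 0.95 |
| 0.75 | 0.88 | 0.95 |

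With within-site variances in ratio 0.5:1:1:2, the figures at I² 0.50 and 0.75 are 0.90 and 0.86 for DerSimonian-Laird, and 0.94 at both for Hartung-Knapp. The multiplier rises from 1.96 to 3.18, which is 1.62 times as wide for the same standard error.

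**Dependence in the synthetic control pooling.** The between-site correlation r is an assumption. With equal variances, the variance of the pooled mean is multiplied by 1 + (k − 1)r = 1 + 3r:

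| r | True SE / SE assuming independence | DerSimonian-Laird coverage, I² = 0 | Hartung-Knapp coverage, I² = 0 |
|---|---|---|---|
| −0.1 | √0.7 = 0.84 | interval conservative | not simulated |
| 0 | 1.00 | 0.96 | 0.95 |
| 0.1 | √1.3 = 1.14 | 0.93 | 0.92 |
| 0.2 | √1.6 = 1.26 | 0.90 | 0.89 |
| 0.3 | √1.9 = 1.38 | 0.86 | 0.85 |
| 0.5 | √2.5 = 1.58 | 0.79 | 0.75 |

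A small-sample interval therefore does not repair dependence. On calendar time, Study design gives a collection period from November 2012 to March 2020, which is 89 months. Two windows of 49 months must share at least 2 × 49 − 89 = 9 months. The start dates of the units are not given.

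**The case against.** **On configuration.** No formal test of configuration is planned. Varied sites are a sensible choice for generalisability, and a descriptive comparison of four units is useful. All of this stands. It is also fair that 0 degrees of freedom applies to the features taken jointly, since one feature alone leaves 2. But site effects estimated precisely enough to differ would show only that sites differ, not which feature is responsible, so the wording still claims too much. The Discussion's sentence about commissioners does not itself mention configuration, so configuration advice should not be described as a promised product for them.

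**On pooling.** A reader might infer three stronger things that the document does not support.

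- *That four sites cannot be pooled at all.* With independent estimates, the Hartung-Knapp interval keeps about 95% coverage.
- *That the pooled intervals will be too narrow.* The text says the model accounts for heterogeneity, which points away from a fixed-effect analysis. It names no between-site variance estimator and no z-interval. Those choices are commonly left to an analysis plan, and their absence here is not a fault.
- *That the site estimates share control trusts.* The ITS fits use no controls. In the synthetic control study, subsets are selected for each treated trust and overlap is not stated. One donor pool and three inner-city sites make overlap plausible, not certain. A national shock falling after one unit opened but before another did could push their estimates in opposite directions, so even the sign of the correlation is open.

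**Conclusion.** The claim that the study can ascertain an optimal configuration does not hold. It follows from Table 1 alone, with no assumption about effect sizes: four sites, at least four features, no pair isolating one of them, 0 residual df jointly and 2 df for a single feature.

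The two pooling points are conditional. The loss of coverage to about 88–91% applies only if a z-based DerSimonian-Laird interval is used and I² is 50–75%. The dependence point applies only if control subsets overlap or the estimates are otherwise correlated; the range of r shown is illustrative. Neither shows that the planned pooled analysis is wrong. The site-level analyses are unaffected.

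**What to change.** 1. Delete the optimum-design wording under Study setting and in the Discussion. State that differences between sites in configuration are descriptive and hypothesis-generating only. This is an edit to the text that withdraws one claim and changes no analysis.
2. For the pooled ITS effect, specify a random-effects model with an interval suited to few sites, such as Hartung-Knapp with t on 3 df, shown beside the four site estimates already planned. The cost is a wider interval.
3. For the synthetic control study, report which control trusts are used for which treated trust. If subsets overlap, do not pool the estimates as independent. Estimate their between-site covariance, for example with a bootstrap that redraws shared control trusts once for all sites, and use it in the pooled standard error. This needs some programming but keeps the selection of controls for each trust. If no subsets overlap, a sentence saying so settles the shared-control question.

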### Synthetic control study

We will use the Generalised Synthetic Control (GSC) method [50] to compare the outcomes of patients attending a treated trust after the introduction of a PDU, to that of patients attending selected control trusts. The GSC method is in the spirit of a traditional synthetic control method in that it effectively re-weights the controls units to create a so-called ‘synthetic control’ that has similar values of the outcomes and covariates in the pre-intervention period. The idea is that this similarity is assumed to extend into the post-intervention period, providing an estimate of the outcomes that would have been expected at the trust if the PDU had not been introduced. These are referred to as the counterfactual outcomes.

The approach is as follows. For each treated trust, we first select a subset of the available control trusts that are as ‘similar’ as possible to the treated trust in the period prior to the introduction of the PDU. Similarity will be assessed in terms of variables such as attendances, deprivation, patient profile and location profile, e.g. by using the NHS TRUST Peer-Finder Tool [51]. The GSC method then uses the data from the selected control group, as well as the pre-intervention data from the treated trust, to estimate a synthetic control, and hence the counterfactual outcomes for the treated unit. The difference between these counterfactual outcomes and the observed outcomes in the treated unit in the period following the introduction of the PDU is assumed to provide estimates of the causal impact of the PDU on the outcomes in the treated unit. The precision of estimates will be assessed using parametric bootstrap procedures as described in [50] to generate *P*-values and confidence intervals.

Estimates will be risk-adjusted for variables that reflect changes over time in the characteristics of the denominator population, i.e. those who are able to have the outcome. For example, when looking at the rate of ED psychiatric presentations per 1000 trust catchment, the characteristics of the trust catchment population are relevant; when looking at the proportion of 4-h psychiatric ED breaches, the characteristics of psychiatric ED presentations are relevant. Estimates of overall effect will be made using the same methods as described for the ITS analysis.

### Sensitivity analysis to other changes on the crisis care pathway

To account for potential confounding of any identified service reconfiguration or changes to models of care, an ITS sensitivity analysis comparing the months following the introduction of PDUs to the same period prior to the identified service change will be administered. These data will be used in interpreting time series curves for each of our outcomes (for example, where reconfiguration of community services was followed by a temporary spike in inpatient admissions, or where the introduction of a street triage service coincided with a sustained reduction in presentations at the ED).

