### Data collection

#### Interrupted time series

Outcome data will be collated as time series for 24 months pre- and 24 months post-implementation of the PDU. All data will be aggregated to a single observation at multiple time points at equal intervals. In our case, depending on the variable under study, the time series aggregation unit will be weeks or months. For out of area admissions, for example, a weekly total may be too low to appropriately use a weekly time series as differences may reflect random variation rather than a real effect (i.e. a high noise-signal ratio). The aggregation unit used will be the one that provides proportionately better model fits. Aggregated service use data over the relevant 4 years will be sourced locally from mental health trusts and the ED (acute hospital trusts) of participating PDU sites, as detailed above, through contact with Information Management & Technology (IM&T) departments at each trust. Where a substantial proportion of PDU patients (≥ 25%) are referred from a second acute trust, we will use data from that trust also. All data is handled in accordance with the UK Data Protection Act 2018 (incorporating the EU20 General Data Protection Regulation). Information Management Services personnel within the NHS Trusts will collate the trustwide service use data required for study analyses. Electronic transfer of this data between NHS Trusts and the lead university (St George’s, University of London [SGUL]) will be by encrypted email transfer. This data does not include personally identifiable information and will not be shared by SGUL with any third party or linked with other data that might render the information more identifiable. All data held on NHS or university computers will be securely held on password protected servers and not on individual PCs. The datasets generated during and/or analysed during the current study will be stored in a non-publicly available repository.

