#### Key informant interviews

Semi-structured interviews (*n* = 5 per site) will be held with strategic managers in each site, including PDU manager, Acute Care Pathway lead, mental health lead commissioner (or their equivalent locally) and the ED manager and ED clinical director at the main general hospital at each site. Interviews will seek to identify any changes to the crisis care pathway within the duration of the time series, including the introduction or withdrawal of services or new initiatives, including provision of services outside of the NHS mental health trust (e.g. by third sector agencies), changes in policy or protocol relating to the assessment and managing of psychiatric presentation to ED and seasonal impacts.

To account for potential confounding of any identified service reconfiguration or changes to models of care, sensitivity analysis comparing the months following the introduction of PDUs to the same period prior to the service change will be administered. These data will be used in interpreting time series curves for each of our outcomes (for example, where reconfiguration of community services was followed by a temporary spike in inpatient admissions, or where the introduction of a street triage service coincided with a sustained reduction in ED presentation).

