## Discussion

Whilst the ITS method is suitable for assessing the impact of large organizational changes, it is important to plan how to address potential limitations. The biggest challenge to the study is from both national and local changes to the crisis care pathway (and service use) independent of the introduction of the PDUs during the study period. We will be constructing a detailed timeline of the crisis care pathway for each site, gathering data about any changes and the dates of these changes. Where the effect of the changes can be numerically estimated, the impact of these effects will be investigated using a sensitivity analysis.

The supplementary synthetic control study will control for national changes and trends over the 4 year period studied by contrasting outcomes in the treated trust with outcomes from trusts elsewhere in England with similar characteristics to the treated trust, but which do not have a PDU. This is achieved by creating a synthetic control that is assumed to provide an estimate of the hospital use that would have been expected at the treated trust in the absence of the introduction of the PDU. However, it is possible that the synthetic control is inappropriate, and not reflective of the treated trust before the PDU was introduced, nor of how it might have behaved afterwards. If this is the case, then our findings might be due to systematic differences between the treated trust and the synthetic control, rather than changes in how care was delivered. In the absence of a randomized controlled trial, it is not possible to eliminate this risk but the study is designed to reduce it as much as possible by using a control group with trusts that have similar characteristics to the treated trust, using risk adjustment to take account of any differences in the patients using hospital services over time and running additional sensitivity analyses to confirm that findings are robust to changes in the number of trusts in the control group and number of pre-intervention time periods used to determine the synthetic control.

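### The sensitivity analysis for other service changes does not remove a lasting change that came before or with the PDU: its contrast returns the PDU effect plus that change's full effect

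*Protocol article*

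**What the plan says.** The section on sensitivity to other pathway changes states its purpose: "To account for potential confounding of any identified service reconfiguration or changes to models of care, an ITS sensitivity analysis". It then defines the analysis as "comparing the months following the introduction of PDUs to the same period prior to the identified service change". The section on key informant interviews gives the same rule almost word for word, without the word 'identified': "comparing the months following the introduction of PDUs to the same period prior to the service change".

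Both sections give two examples of what they have in mind. One is a short-lived rise in admissions after community services were reorganised. The other is lasting: "where the introduction of a street triage service coincided with a sustained reduction in presentations at the ED".

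The Discussion ranks the threat: "The biggest challenge to the study is from both national and local changes to the crisis care pathway". It adds: "Where the effect of the changes can be numerically estimated, the impact of these effects will be investigated using a sensitivity analysis". No estimator is attached to that sentence. The synthetic control study is credited there with controlling national changes and trends.

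The ITS analysis section lists a prior trend, a level change and a slope change at the PDU date. It lists no term for any other dated change.

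**The concern.** A sensitivity analysis for confounding should hold the confounder fixed or model it. Here the reference window lies before the other change, while the comparison window lies after the PDU. If the other change persists and was in place by the time the unit opened, the two windows differ in both respects, and the contrast attributes the whole difference to the PDU. It also sets aside the months between the two dates, which are the ones that could tell the effects apart.

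At stake is the reading of site-level results, and through them the pooled effect, on outcomes such as ED psychiatric presentations. A lasting street-triage effect on that primary outcome is the plan's own example. Interviews are already planned to date such changes, so the data for a better analysis will be there.

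**Working it through.** **The plan's own figure.** The article gives no number for this analysis. Its only power figure (above 99% for 208 time points) has no bearing on it.

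**Inputs.** The series has 24 months each side of opening (data collection section: "Outcome data will be collated as time series for 24 months pre- and 24 months post-implementation of the PDU"). The windows are those in the quoted rule. Assumed, because the documents give no effect sizes: baseline B, no trend, no noise, PDU step P at month 0, and another lasting step C at month k.

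**Change before or with the PDU (k ≤ 0).**
- Mean after the PDU = B + P + C.
- Mean before the other change = B.
- Contrast = P + C, whatever the sizes and whatever window length is used.

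**Numbers with P = 0 and C = -10.** The target is 0. The contrast is the same as a mean difference over equal windows and as a segmented fit that omits the months between the two dates.

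| Other change before opening | Stated contrast | Main model, unadjusted level change | Model with dated step, level change | SE ratio for level change |
|---|---|---|---|---|
| 12 months | -10.0 | +2.8 | 0.0 | 1.08 |
| 6 months | -10.0 | -1.6 | 0.0 | 1.02 |
| 3 months | -10.0 | -5.3 | 0.0 | 1.22 |

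The unadjusted slope changes are +0.63, +0.47 and +0.27 per month; with the step term they are 0. The SE ratio compares the model with the step term against the model without it, under independent errors of constant variance. If k = 0, the contrast is again -10.0, and the step term coincides with the PDU term, so no within-site model can separate them.

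**A non-zero PDU effect.** With P = -10 and C = -6, the contrast is -10 + (-6) = -16.0 for changes 18, 12 or 6 months before opening. The dated step model gives -10.0.

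**Change after the PDU (k > 0), post-PDU months not cut.** The 24 months before the change contain k months with the PDU open.
- Post-PDU mean = B + P + C(24 - k)/24.
- Reference mean = B + P·k/24.
- Contrast = (P + C)(24 - k)/24.

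With P = 0 and C = -10, this is -10 × 18/24 = -7.5 at k = 6 and -10 × 12/24 = -5.0 at k = 12. Truncating the series at the change, or adding the dated step, gives 0.0.

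**Temporary disturbance that ended before the PDU.** Take P = 0 and a rise of +10 that stops before opening.

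| Months of the rise | Main model level change | Stated contrast | Model with a lasting step added |
|---|---|---|---|
| -6 to -4 | -3.7 | 0.0 | -4.7 |
| -6 to -1 | -8.4 | 0.0 | -10.0 |

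Here the stated contrast is right, and a lasting step term makes matters worse. The shape of the added term has to match the shape of the change.

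**The case against.** The strongest defence is that this is one condensed sentence about a supporting analysis, used to help interpret the curves. No primary estimate, pooled effect or sample size depends on it, and an unseen analysis plan may spell it out. That limits the weight of the point. It does not remove it, because the article states a specific contrast with a specific purpose, and for lasting earlier changes the contrast does not serve that purpose.

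The wording also allows other readings. A reader could take it to mean that post-PDU months are cut at a later change. That would be sound for later changes, but neither section says it, and it does nothing for an earlier one. In the interview section, where 'identified' is missing, the service change could be taken as the PDU itself. The comparison would then be an ordinary before-and-after one with no adjustment at all.

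Four stronger readings are tempting, and the documents do not support them.
- *The contrast never isolates the PDU.* It does so for a temporary disturbance that ended before opening, which is the plan's first example.
- *It would falsely confirm the main result.* In the illustration the main model gives +2.8, -1.6 or -5.3 against -10 from the contrast. Outside the coincident case, the two would visibly disagree.
- *It is the only numerical protection.* The Discussion promises a sensitivity analysis where effects can be estimated, without fixing a method, and assigns national changes to the synthetic control.
- *The synthetic control can stand in for it.* A change local to the treated trust is absent from its control trusts, so it stays in the difference. The Discussion claims control only of national changes and trends.

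**Conclusion.** The point holds for lasting changes. If such a change came before or with the PDU, the stated contrast equals the PDU effect plus the whole of the other effect. This is algebra and does not depend on the assumed sizes; it requires only that the other effect persists into the post-PDU months. With a true PDU effect of 0 and another step of -10, the answer is -10.0. For a lasting change after opening, part of the other effect can remain, because the text sets no cut-off: -7.5 or -5.0 in the same illustration, assuming 24-month windows. For a temporary disturbance over before opening, the contrast is correct.

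The defect is in a supporting analysis. It would mislead the interpretation of affected sites and leaves the planned primary model as it is. The effect sizes are illustrative, and the standard-error ratios assume uncorrelated errors.

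**What to change.** Replace the rule in both sections that state it (key informant interviews; sensitivity analysis to other pathway changes) with the following.

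1. For each dated change found at interview, add a term of matching shape to that site's segmented regression. Use a step for a lasting change, with a slope if it was gradual. For a temporary one, use a pulse or omit the affected months.
2. Report the PDU level and slope change with and without the term.
3. For a change after opening, also refit with the series truncated at that date.
4. Where a change coincides with the opening or falls too close to it, report that the site's ITS cannot separate the two effects. Do not cite the synthetic control as resolving a local change.

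The cost is revised wording and a few extra fits, using dates already being collected. The PDU level change becomes somewhat less precise: its standard error rises by about 2%, 8% and 22% for a step 6, 12 and 3 months before opening in the illustration.
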